**Reporting**

The PI will be responsible for drafting the report of this study in collaboration with the epidemiologist of MSF HQ. Publication in an appropriate medical scientific journal will be sought. The PI is responsible for ensuring the collaboration and consent of all co-workers, including the epidemiologist and for submitting an agreed version of the final report within three months of completion of the study.

# 11. ETHICAL CONSIDERATIONS

Ethical considerations are fundamental to the design of any research involving human beings, and have been taken into consideration throughout the design of this study.

**Cooperation with national and local partners** in Katanga Province, DRC:

For this study, cooperation is established with the National Health Authorities in Kilwa (Médecin Chef de Zone) and the Province (Médecin Inspecteur Provincial of Katanga), who is a member of the study group. MSF-OCA feels this cooperation is essential for accessing and providing information to the key decision makers involved in the definition of effective measures to combat malnutrition. The local administrative authorities will be consulted about the nature and time-schedule of the planned study.

The details of the study and its implications will be explained to health staff in the clinics in the area. As the study involves a temporary benefit (RUTF) for the treatment of the study group it is essential that community members understand the purpose of the investigation and agree with the procedures. MSF-OCA field visitors will inform village chiefs and community members (specifically women with young children).

**Benefits to the community**: Based on the outcome of this study MSF will consider adapting protocols to include provision of RUTF for children with serious acute illness. If shown to be effective, this would contribute to improving survival of children in the community, as assumed is that improved nutrition in general will improve survival. The study also hopes to contribute to an improved understanding in the community of the necessity for good nutrition after an acute infection. The opportunity will be taken to instruct as many doctors and nurses as possible in the importance of good nutrition after an infection and the impact on growth of disease.

**Potential risks:** Plumpynut® is safe for children with malaria. Although research has suggested that iron supplementation during an episode of malaria can negatively influence the outcome of the disease[[28]](#endnote-25), the iron content in Plumpynut® (5 mg iron /sachet) is not considered as a major problem, as it is much lower than normally used therapeutic doses (3 mg/kg/day). Food based delivery of iron has substantially different patterns of absorption and metabolism compared to iron supplementation through pills. [[29]](#endnote-26) In addition, in this study, malaria will be treated immediately upon admission, and thus any potential effect of iron in the food on the parasite will be very limited.

**Scientific merit:** There are substantial gaps in knowledge and evidence relating to the effectiveness of providing nutritional support on acute illness and convalescence. There is an urgent need to investigate whether a short nutritional intervention can achieve complete nutritional recovery. The design and conduct of this pilot study aims to start to answer some of those evidence gaps in a robust way in a field setting.

**Informed consent:** Parents/guardians of the patients will be informed about the purpose of the study, the procedures when participating in the study, and asked for their consent. Informed consent forms will be translated into local languages and back-translated; they will be piloted for comprehension in the field. As a significant proportion of the population is not literate, the consent form will be read out to the patient’s parent/guardian to obtain oral consent as required (see annex 1).

It will be made clear that participation is voluntary and that patients will receive the same standard of medical treatment for malaria whether or not they agree to participate in the study. Patients can withdraw from the study when they wish at any point.

**Confidentiality:** The medical examinations and the interviews will be performed in private (a separate room) to ensure patient confidentiality. Patient data will be only accessible to the investigators and not given to any unauthorized person. In further data processing, patient data will be anonymous, and only given study sequential numbers.

Optimal medical treatment:

Decisions regarding the management of patients will be based on their clinical condition, independent of the study. Participation in the study will not, at anytime, preclude supplementary treatment or a change in therapy if clinically indicated. The well-being of the patient will always be a priority over participation in the study. Directly observed treatment for malaria medication is chosen to ensure optimal compliance with treatment.

**Feedback of results:** The individual results of weight change will be shared and discussed with the caretaker. At the end of the study, feedback and preliminary outcomes will be provided to the stakeholders in the community and to medical authorities.

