# 3. STUDY DESIGN AND METHODS

**3.1 Study design**

The study design is that of a randomised intervention study. Children with confirmed *P. falciparum* malaria, meeting all study inclusion criteria, will be enrolled in the study for a period of 28 days. Participants will be assigned at random to either the intervention or the control group.

The intervention group will receive treatment for malaria plus 1 bag of RUTF per day for 14 days. The control group will receive treatment for malaria without provision of RUTF.

Random allocation to either intervention or control group is thought to be acceptable by the population as RUTF is seen as a medicine rather than a food item. A similar study did not meet a problem with randomisation.[[18]](#footnote-2) For other illnesses, the participants will be offered medical treatment according to the best local standards.

Follow-up visits will be scheduled for directly observed treatment for malaria (day 0, 1 and 2), malaria parasite density and clearance (D0, D2, and until slide is negative; and for weight measurements at day 0, 1, 13 and 27. Weight will be measured twice at each visit by two independent observers. A detailed questionnaire will be conducted at the start, and at day 13 and 27.

All participants who attend follow up sessions at the clinic will receive a small incentive[[19]](#footnote-3)* in order to compensate for lost time due to participation in the study (RUTF will not be given to the control group at the end of the study).

The study will be conducted in the period (May-June) that is likely to have a stable prevalence of malnutrition, a stable incidence of *P. falciparum* malaria and other morbidities (e.g. pneumonia and diarrhoea). The total duration of the data collection will be 2 months for data gathering: 4 weeks of enrolment (40 participants per week) and 4 weeks of follow up (the last follow-up being done 4 weeks after the last enrolment).

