**4.2 Outcome parameters:**

**Main outcome:**

Average weight gain (g/kg/day) in the intervention group from day 1 to day 14 will be compared with the average weight gain in the control group.

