**Secondary outcomes:**

- Proportion of children having lost weight in each group
- Sustained weight gain compared to short term weight gain (as assessed at 2 weeks after completion of the supplementation period (i.e. 4 weeks post intervention)
- Contributing factors for weight change (see details of potential confounders/effect modifiers in the following section).

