**6.2 Day 14 after treatment**:

At day 14 a further questionnaire (see annex 4) will be administered, in addition to anthropometry measurements and repeat medical examination:

- Anthropometry: weight, MUAC, oedema
- Medical status: fever, appetite, intercurrent illnesses,
- Laboratory data: thick blood film and level of parasitaemia
- Medical history: duration of symptoms, new illnesses.

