**7.4 Malaria treatment**

## In order to achieve a similar compliance with malaria treatment in the two study arms, directly observed malaria treatment will be implemented in both groups.

## Children will remain under observation for 30 minutes after treatment to ensure they don’t vomit their medication. If they do vomit the medication within 30 minutes, the same treatment regimen will be given again and children will again remain under observation for 30 minutes.

Parasite clearance will be monitored by blood slide readings on D2. Treatment failure will be assessed on D2, including parasitaemia higher than D0 count. In the case of treatment failure, a 2nd line treatment regimen will be used, as per local MSF treatment protocols. These children will be withdrawn from the study.

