**7.5 Laboratory examination and quality control**

Extra training will be given to the laboratory staff about the rationale and methods of the study. MSF standard procedures for laboratory quality control will be applied. Routinely a thick blood film will be taken at D0 (after the result of the paracheck**®** test is positive) D2 and D13.

Blood films will be examined to determine the presence and the density of falciparum parasites. Slide results will be recorded in ‘number of parasites per microlitre (#/µL)’ and further be rated :+ =1-10 parasites per 100 thick film fields

++ =11-100 parasites per 100 thick film fields

+++ =1-10 parasites per single thick film field

++++ = more than 10 parasites per single thick film field

During the first 3 days of the study 20% of blood slides will be reread by a second microscopist. All weak positive slides will be crosschecked. Discrepant results will be assessed and clarified amongst the two available microscopists. All blood slides will be appropriately stored for future external QC; normal MSF quality control procedures will be implemented: 10% of the slides will be referred to a reference lab (PathCare in Nairobi) for cross-checking. This sample of 10% should show 100% agreement. If not, then all slides will be crosschecked.

Haemoglobin levels will only be assessed when anaemia is clinically suspected, as is the current clinical procedure.

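### The risk that iron worsens malaria is named, but no stated outcome compares parasitaemia or treatment failure by arm, and the sections disagree on whether every child has a day 13/14 film

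*Protocol*

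**What the plan says.** **The risk.** Under Potential risks, section 11 says that "research has suggested that iron supplementation during an episode of malaria can negatively influence the outcome of the disease". It sets this aside for three reasons: the dose is low, iron in food behaves differently from iron in pills, and malaria is treated at once.

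**The outcomes.** In 4.2 the main outcome is "Average weight gain (g/kg/day) in the intervention group from day 1 to day 14", compared with control. The secondary outcomes are "Proportion of children having lost weight in each group", sustained weight gain and factors contributing to weight change. The synopsis list is similar. The analyses in section 10 concern weight change and the proportion gaining weight.

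**The films.**
- 3.1 plans visits for "malaria parasite density and clearance (D0, D2, and until slide is negative".
- 6.2 lists, for the day 14 visit, "Laboratory data: thick blood film and level of parasitaemia".
- 7.5 describes a routine film at day 0 (once the rapid "test is positive) D2 and D13").
- The activity schedule (Annex 7) shows two unconditional blood-slide marks and one entry that depends on the day 2 slide.
- 6.3 lists no film at day 28.

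**Treatment failure.** 7.4 says "Treatment failure will be assessed on D2, including parasitaemia higher than D0 count". These children move to second-line treatment and leave the study.

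**The concern.** Two separate defects meet here.

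First, the protocol names a biological risk of the randomised product, gives reasons why it should be small, and collects data that bear on it, but defines no comparison that uses those data. Sections 1.3 and 11 say that the sponsor would consider routine supplementation after serious infections if the result is favourable. A report confined to the stated outcomes would then show weight alone.

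Second, a child who is clear on day 2 has a day 13/14 film under two sections and none listed under the other two. If staff follow 3.1 or the activity schedule, parasitaemia after a negative day 2 film is not observed, and no later analysis can recover it. If practice varies between children, the films that exist are a selected set.

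**Working it through.** The plan gives no figure on this point, so the main check sets the sections side by side.

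**Film schedule for a child negative on day 2** (day 13 and day 14 are taken as the same visit)

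| Source | Day 0 | Day 2 | Day 13/14 |
|---|---|---|---|
| 3.1 | yes | yes | not listed; the series ends at the first negative slide |
| 6.2 | – | – | yes |
| 7.5 | yes | yes | yes, routine |
| Activity schedule | two unconditional marks in all | | only an entry conditional on day 2 |

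The column positions of the activity schedule are not legible in the copy reviewed. The count is enough: two unconditional marks cannot cover three routine films. Without that table, 3.1 still differs from 6.2 and 7.5.

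**Use of the films.** The synopsis, 4.2 and section 10 contain no parasitological, treatment-failure or other safety comparison. Section 5 does not list parasite density among the factors to be measured.

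**Who would be missing.** 7.4 withdraws day 2 treatment failures, the children in whom the named harm could show first. 3.2.3 withdraws children who develop an exclusion criterion, and 3.2.2 includes signs of severe malaria among these. It also withdraws children for low sachet consumption, which can occur only in the supplement arm. No count of withdrawals by arm is stated. A table of day 13/14 films in the remaining children would therefore rest on denominators selected differently in each arm.

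**What a comparison could show.** Inputs:
- Children per arm: 3.3 proposes 100. Two routes give 80: 40 per week × 4 weeks ÷ 2 arms (3.1), or 100 × (1 − 0.20), using the 20% loss assumed in 3.3.
- Film positivity of 5% and 10%: assumed, as the protocol gives no rate.

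Half-width of the 95% interval for the difference, with equal rates: 1.96 × √(2p(1 − p)/n).
- n = 80, p = 0.10: 1.96 × √(0.18/80) = 0.093
- n = 80, p = 0.05: 1.96 × √(0.095/80) = 0.068
- n = 100, p = 0.10: 1.96 × √(0.18/100) = 0.083
- n = 100, p = 0.05: 1.96 × √(0.095/100) = 0.060

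Power of a two-sided 5% test, with p̄ the mean of the two rates: Φ{[|p1 − p2| − 1.96√(2p̄(1 − p̄)/n)] / √[(p1(1 − p1) + p2(1 − p2))/n]}.

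| Assumed rates | 80 per arm | 100 per arm |
|---|---|---|
| 5% v 10% | 22% | 27% |
| 5% v 15% | 56% | 66% |
| 10% v 20% | 42% | 51% |
| 5% v 20% | 82.5% | 90% |

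The comparison is therefore suited to estimation, not to a test.

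**A related discrepancy.** One of the three reassurances is that "the iron content in Plumpynut® (5 mg iron /sachet) is not considered as a major problem". Annex 6 gives 10.6 mg per 92 g ration, and 10.6/5 = 2.1 times as much. The two passages must be reconciled. The present point does not depend on which is correct.

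**The case against.** The strongest reply has four parts.

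1. **The schedule.** 6.2 and 7.5 are the operative sections and they agree. 3.1 is an overview of clearance monitoring and does not forbid a later film. The activity schedule is weak evidence: it also shows a single mark for the anthropometry row, although 6.2 and 6.3 repeat MUAC and oedema. This narrows the defect to a reconciliation of text but does not remove it, because someone working from 3.1 or the activity schedule would not take the film that 7.5 calls routine.

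2. **The analysis plan.** Tabulating laboratory results by arm is often left to the SAP, which was not available. A reader might infer that excess parasitaemia with the supplement is bound to go unreported. The protocol does not establish that. It shows only that no stated outcome covers it. The schedule conflict does not cause the gap either: it would exist under a consistent schedule.

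3. **Other data.** A reader might also infer that poor weight gain from recurrent malaria could not be told from non-response to the supplement. That goes too far. Section 5 measures incident disease, the visits in 6.2 and 6.3 record fever and intercurrent illness, and Annex 4 asks about fever, facility visits, medication and recovery. Without a film these are imperfect, but they are not absent.

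4. **Individual care.** Directly observed treatment, the day 2 check and second-line treatment protect each child. This stands. The point concerns comparison between arms and does not suggest that children are left unmonitored.

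**Conclusion.** Both facts hold. The protocol names a possible harm of the randomised food and states no comparison by arm that bears on it, and its sections disagree on the day 13/14 film. The change is worth making because films after enrolment are already planned and a film not taken cannot be recovered.

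The size is limited. With 80 per arm and 5% to 10% positivity, both assumed, the interval for the difference is about ±7 to ±9 points. With 10% positive in each arm and no observed difference, an excess of about 9 points, close to a doubling, would remain compatible with the data. A reader might hope that the comparison would settle the safety claim in section 11. It cannot: it could exclude a large difference only. Nor do the documents show that the supplement worsens malaria.

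**What to change.** 1. Reconcile the follow-up film schedule across 3.1, 6.2, 7.5 and the activity schedule, so that it is clear which films are taken in every child and which are conditional.
2. Add to 4.2 and section 10 a descriptive safety outcome by arm, with difference and 95% confidence interval: treatment failure on day 2, and film positivity and parasite density at each follow-up film that the reconciled schedule takes in all children.
3. Count children withdrawn under 7.4 and 3.2.3 by arm and reason. Keep day 2 failures as events in the randomised denominator, and report later films that are missing.
4. State in advance that the comparison can exclude only a large difference, and give the assumed rates and numbers behind that statement.
5. Have section 11 refer to this outcome, so that it no longer rests on the assertion alone.

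The cost is wording in a few sections and one extra descriptive table with wide intervals. No new visit is needed, since 6.2 and 7.5 already place a film at the day 13/14 visit. If the schedule is reconciled without that film, the table covers only the films that every child has.

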## Follow up of children with a disease who are excluded from the study

- Illnesses in children with or without malaria presenting to the clinic will be treated according to the best standards available to MSF in that community.
- Children with severe malnutrition will be referred to the existing MSF Therapeutic Feeding Program (TFP) to be treated adequately. The 2005 WHO growth standards will be applied, ensuring that all children at risk for mortality related to malnutrition will be selected for therapeutic feeding.

**Independent review:** The Ethical Review Board of MSF will review the study protocol. Up to now there has been no appropriate ethical review committee identified in Katanga. Permission from local authorities in the districts of study will be obtained.

| Annex 2: RUTF malaria recovery study | | | | | | | | | | | | |
| --- | --- | --- | --- | --- | --- | --- | --- | --- | --- | --- | --- | --- |
| Checklist for inclusion/exclusion | | | | | | | | | | | | |
|  | | | |  | |  | | |  |  | |  |
| Paracheck number | | | |  | |  | | |  |  | |  |
| Paracheck positive: | | | | Yes |  | ** Continue** | | |  |  | |  |
|  | | | | No |  | ** Do not enrol in the study** | | | | | | |
|  | | | |  | |  | | |  |  | |  |
| Child between 6 months and 5 years old? | | | | Yes |  | ** Continue** | | |  |  | |  |
|  | | | | No |  | ** Do not enrol in the study** | | | | | |  |
|  | | | |  | |  | | |  |  | |  |
| Date (dd/mm/yy): | | | |  | |  | | |  |  | |  |
|  |  | | |  | |  | | |  |  | |  |
| **A. Danger signs / severe malaria:** | | | | | | | | |  |  | |  |
|  | 1. Unable to drink/breastfeed | | | | | | | |  | Y | | N |
|  | 2. Vomiting everything | | | | |  | | |  | Y | | N |
|  | 3. Recent history of convulsions | | | | | | | |  | Y | | N |
|  | 4. Unable to sit or stand | | | | |  | | |  | Y | | N |
|  | 5. Any other signs of severe malaria (if yes, specify) | | | | | | | | | Y | | N |
|  |  | | |  | |  | | |  |  | |  |
|  | **Any of the questions above answered with Yes?  Do not enrol in the study and refer for immediate treatment** | | | | | | | | | | | |
|  |  | | |  | |  | | |  |  | |  |
| **B. Signs of anaemia** | | | | | | | | |  |  | |  |
|  | 1. Some or severe palmar pallor | | | | | |  | |  | Y | | N |
|  | 2. Mucous membrane pallor | | | | |  | | |  | Y | | N |
|  | 3. Respiratory distress | | | | |  | | |  | Y | | N |
|  |  | | | | | | | | |  | |  |
|  | **Any of the questions above yes? Test Hb; HB<5 g/dL?  Do not enrol in the study and offer normal treatment** | | | | | | | | | | |  |
|  |  | | |  | |  | | |  |  | |  |
| **C. Severe malnutrition** | | | | | | | | | | | | |
|  | 1. Bilateral oedema | | | | | | | Yes | | **No** |  | |
|  | 2. MUAC < 11 cm | | | | | | | Yes | | **No** |  | |
|  | 3. Weight-for-Height < -3sd WHO 2005 reference | | | | | | | Yes | | No |  | |
|  |  | | |  | |  | | |  |  | |  |
|  | **Any of the questions above answered with Yes?  Do not enrol in the study and refer for immediate treatment in the TFP** | | | | | | | | | | | |
|  |  | | |  | |  | | |  |  | |  |
| **D. Other criteria - please tick:** | | | | | |  | | |  |  | |  |
|  | 1. Serious concomitant illness | | | | |  | | |  | Y | | N |
|  | 2. History of allergy to anti malarial drugs | | | | | | | |  | Y | | N |
|  | 3. History of allergy to peanuts or milk | | | | | | | | | Y | | N |
|  | 4. Exclusive breastfeeding | | | | | | | | | Y | | N |
|  | 5. Sibling enrolled in this study | | | | | | | | | Y | | N |
|  | 6. Lives further away than 30 min walking distance | | | | | | | |  | Y | | N |
|  | (check name of village) | | | | | | | |  |  | |  |
|  | **Any of the questions above answered with Yes?  Stop** | | | | | | | | | | |  |
|  |  | | |  | |  | | |  |  | |  |
| **E. Consent:** | | | | | | | | |  |  | |  |
| *Explain the study and read out consent form* | | | | | | | | |  |  | |  |
|  | Guardian > 18 and close relative, gives consent | | | | | | | |  | Y | | N |
|  | |  | | | | | | |  |  | |  |
| Included? | Y | | N |  | | | | |  |  | |  |
|  |  | |  |  | | | | |  |  | |  |
| Study ID number |  | |  |  | | | | |  |  | |  |

# *Consent forms are presented in Annex 1.*

| Annex 3: RUTF for malaria recovery study |
| --- |
| **Intake questionnaire upon enrolment** |

| Date (dd/mm/yy): |  |  | | | |  | |  |  | |  | | | |  |
| --- | --- | --- | --- | --- | --- | --- | --- | --- | --- | --- | --- | --- | --- | --- | --- |
| Patietn ID |  |  | | | |  | |  |  | |  | | | |  |
|  |  |  | | | |  | |  |  | |  | | | |  |
|  |  |  | | | |  | |  |  | |  | | | |  |
|  |  |  | | | |  | |  |  | |  | | | |  |
| Sex | Male | | Female | | |  | |  |  | |  | | | |  |
|  |  |  | | | |  | |  |  | |  | | | |  |
| **Part 1: Questions concerning your child** | | | | | | | |  |  | |  | | | |  |
|  |  |  | | |  | | |  |  | |  | | | |  |
| 1. What is the exact age of your child? | | | | | | | |  |  | |  | | | |  |
|  |  | Birth date of child (dd/mm/yy) | | | | | |  |  | |  | | | |  |
|  | ***Or*** | Age of child (months, years). | | | | | |  |  | |  | | | |  |
|  |  |  | | |  | | |  |  | |  | | | |  |
| 2 You have brought your child because he/she is ill. How many days ago did this episode of illness start? | | | | | | | | …… | days | |  | | | |  |
|  |  |  | | |  | | |  |  | |  | | | |  |
|  | | | | | | | |  |  | |  | | | |  |
| 3. Has your child been ill with a fever at any time in the last 2 weeks? | | | | | | | | Yes |  | |  | | | |  |
|  |  |  | | |  | | | No |  | |  | | | |  |
|  |  |  | | |  | | | Don’t know |  | |  | | | |  |
|  |  |  | | |  | | |  |  | |  | | | |  |
|  |  |  | | |  | | |  |  | |  | | | |  |
| 4. Has your child had an illness with cough at any time in the last 2 weeks? | | | | | | | | Yes |  | |  Q 5 | | | |  |
|  |  |  | | |  | | | No |  | |  Q 7 | | | |  |
|  |  |  | | |  | | | Don’t know |  | |  Q 7 | | | |  |
|  |  |  | | |  | | |  |  | |  | | | |  |
|  |  |  | | |  | | |  |  | |  | | | |  |
| 5. When your child had an illness with a cough, did she/he breathe faster than | | | | | | | | Yes |  | |  Q 6 | | | |  |
| usual with short, rapid breaths or have difficulty breathing? | | | | | | | | No |  | |  Q 7 | | | |  |
|  |  |  | | |  | | | Don’t know |  | |  Q 7 | | | |  |
|  |  |  | | |  | | |  |  | |  | | | |  |
| 6. Was the fast or difficult breathing due to a problem in the chest or | | | | | | | | Chest only | | |  | | | |  |
| to a blocked or runny nose? | | | | | | | | Nose only | | |  | | | |  |
|  |  |  | | |  | | | Both | | |  | | | |  |
|  |  |  | | |  | | | Don’t know | | |  | | | |  |
|  |  |  | | |  | | | Other; specify | | |  | | | |  |
|  |  |  | | |  | | |  |  | |  | | | |  |
| 7. Has your child had diarrhoea in the last 2 weeks? | | | | | | | | Yes |  | |  | | | |  |
| *(Explain the definition of diarrhoea: at least 3 or more liquid stools per day )* | | | | | | | | No |  | |  | | | |  |
|  |  |  | | |  | | | Don’t know |  | |  | | | |  |
|  |  |  | | |  | | |  |  | |  | | | |  |
| 8. In the last 2 weeks, has your child vomited everything? | | | | | | | | Yes |  | |  | | | |  |
| (persistent vomiting several times) | | | | |  | | | No |  | |  | | | |  |
|  |  |  | | |  | | | Don’t know |  | |  | | | |  |
|  |  |  | | |  | | |  |  | |  | | | |  |
| 9. Do you currently breast-feed your child? | | | | | | | | Yes |  | |  Q 10 | | | |  |
|  | | | | | | | | No |  | |  Q 11 | | | |  |
|  | | | | | | | |  |  | |  | | | |  |
|  | | | | | | | |  |  | |  | | | |  |
| 10. How many times during the day did you breastfeed yesterday? | | | | | | | | …… times | | | | | |  |  |
|  | | | | | | | |  | | | | | |  |  |
| 11. **Since your child was ill**, did she/he eat (food or breast milk) | | | | | | | | Much less | | | | | |  |  |
| less then usual, about the same amount, or more than usual? | | | | | | | | Somewhat less | | | | | |  |  |
| IF LESS, PROBE: Was he/she eating much less than usual or somewhat less? | | | | | | | | About the same | | | | | |  |  |
|  | | | | | | | |  | | | | | |  |  |
|  | | | | | | | | Somewhat more | | | | | |  |  |
|  | | | | | | | | Much more | | | | | |  |  |
|  | | | | | | | | Don’t know | | | | | |  |  |
|  | | | | | | | |  |  | | |  | | |  |
|  |  |  | | |  | | |  |  | | |  | | |  |
| **Part 2: The following questions concern yourself or the entire family** | | | | | | | |  |  | | |  | | |  |
|  | | | | | | | |  |  | | |  | | |  |
|  | | | | | | | | Mother | | | |  | | |  |
| 12: What is your relation to the child? | | | | | | | | Father | | | |  | | |  |
|  | | | | | | | | Grandparent | | | |  | | |  |
|  | | | | | | | | Brother /sister | | | |  | | |  |
|  | | | | | | | | Other | | | |  | | |  |
| 13. What is your own age? (years) …………..years | | | | | | | |  | | | |  | | |  |
|  | | | | | | | |  | | | |  | | |  |
| 14. Where (in what village) do you currently live? ………………………………………….. | | | | | | | |  | | | |  | | |  |
|  | | | | | | | |  |  | | |  | | |  |
| 15.How long have you lived in Dubie or surroundings of Dubie? | | | | | | | | Always | |  | |  Q 17 | | |  |
|  | | | | | | | | …… …. | |  | | Years | | |  |
|  | | | | | | | |  |  | |  | | | |  |
| 16. Were you displaced because of the war? | | | | | | | | Yes | | | |  | | |  |
|  | | | | | | | | No | | | |  | | |  |
|  | | | | | | | | Don’t | know | | |  | | |  |
|  | | | | | | | |  |  | | |  | | |  |
| 17. What is the highest level of education that you have completed? | | | | | | | |  |  | | |  | | |  |
| *Please tick the box of the highest level of education* | | | | | | | |  |  | | |  | | |  |
|  |  | No formal schooling | | | | | |  |  | | |  | | |  |
|  |  | 1-4 years of primary school | | | | | |  |  | | |  | | |  |
|  |  | More than 4 years primary school (but not completed) | | | | | |  |  | | |  | | |  |
|  |  | Primary school completed | | | | | |  |  | | |  | | |  |
|  |  | 1-3 years Secondary school (but not completed) | | | | | |  |  | | |  | | |  |
|  |  | Secondary school completed | | | | | |  |  | | |  | | |  |
|  |  | High school | | | | | |  |  | | |  | | |  |
|  |  | College/pre-university/University (but not completed) | | | | | |  |  | | |  | | |  |
|  |  | College/pre-university/University completed | | | | | |  |  | | |  | | |  |
|  |  | Don’t know | | | | | |  |  | | |  | | |  |
|  | | | | | | | |  |  | | |  | | |  |
| 18. What is your current marital status? | | | | | | | |  | | | |  |  | |  |
|  |  |  | | | | | Single |  |  Q 21 | | | | | |  |
|  |  |  | | | | | Currently married |  |  Q 19 | | | | | |  |
|  |  |  | | | | | Cohabiting |  |  Q 19 | | | | | |  |
|  |  |  | | | | | Divorced/Separated |  |  Q 21 | | | | | |  |
|  |  |  | | | | | Widowed |  |  Q 21 | | | | | |  |
|  | | | | | | | |  | | | |  | | |  |
| 19. Is your husband/partner living with you now or is he staying elsewhere? | | | | | | | | Living with her/him | | | |  | | |  |
|  | | | | | | | | Staying elsewhere | | | |  | | |  |
|  | | | | | | | |  | | | |  | | |  |
| 20. What is your husbands’/ partners occupation. That is, what kind | | | | | | | | Agriculture | | | |  | | |  |
| of work does he mainly do? | | | | | | | | Trading/shop | | | |  | | |  |
|  | | | | | | | | Regular job | | | |  | | |  |
|  | | | | | | | | Other , specify | | | |  | | |  |
|  | | | | | | | |  | | | |  | | |  |
| 21. What is your occupation, that is, what kind of work do you mainly do? | | | | | | | | Agriculture | | | |  Q22 | | |  |
|  | | | | | | | | Trading/shop | | | |  Q23 | | |  |
|  | | | | | | | | Regular job | | | |  Q23 | | |  |
|  | | | | | | | | Other , specify | | | |  Q23 | | |  |
|  | | | | | | | |  |  | | |  | | |  |
| 22. Do you mainly work on your own land or on family land, or do you work | | | | | | | | Own land | | | |  | | |  |
| on land that you rent from someone else, or do you work on someone else’s land? | | | | | | | | Family land | | | |  | | |  |
|  | | | | | | | | Rented land | | | |  | | |  |
|  | | | | | | | | Someone else’s land | | | |  | | |  |
|  | | | | | | | |  | | | |  | | |  |
|  | | | | | | | |  |  | | |  | | |  |
| 23. How many hectares of agricultural land do members of this household own? | | | | | | | | None | | | |  | | |  |
| (in total) | | | | | | | | ............ | | | | Hectares | | |  |
| (Household definition: people sleeping in the same house and eating from the same cooking pot) | | | | | | | | Don’t know | | | |  | | |  |
|  | | | | | | | |  |  | | |  | | |  |
| 24. Does any member of your household own | | | |  | | | | Yes | No | | | Don’t know | | |  |
|  | | | | A watch | | | |  |  | | |  | | |  |
|  | | | | A bicycle | | | |  |  | | |  | | |  |
|  | | | | A radio | | | |  |  | | |  | | |  |
|  | | | | Have a generator for electricity | | | |  |  | | |  | | |  |
|  | | | | | | | |  |  | | |  | | |  |
|  | | | | | | | |  |  | | |  | | |  |
| 25. Does this household own any livestock, herds, other form animals, or poultry? | | | | | | | | Yes | | | |  Q26 | | |  |
|  | | | | | | | | No | | | |  Q27 | | |  |
|  | | | | | | | | Don’t | know | | |  Q27 | | |  |
|  | | | | | | | |  |  | | |  | | |  |
|  | | | | | | | |  |  | | |  | | |  |
| 26. How many of the following animals does this household own? | | | | | | | |  |  | | |  | | |  |
|  | | | |  | | | |  |  | | | Number | | |  |
|  | | | |  | | | | Goats | | | |  | | |  |
|  | | | |  | | | | Sheep | | | |  | | |  |
|  | | | |  | | | | Chicken / other poultry | | | |  | | |  |
|  | | | |  | | | | Pigs | | | |  | | |  |
|  | | | |  | | | | Cows | | | |  | | |  |
|  | | | | | | | |  |  | | |  | | |  |
| 27. What is the main material of the external walls of your house? | | | | | | | |  |  | | |  | | |  |
|  | | | |  | | | | Yes | No | | | Don’t know | | |  |
|  | | | | Improvised: plastic, cloth, timber | | | |  |  | | |  | | |  |
|  | | | | Wood, mud, bamboo | | | |  |  | | |  | | |  |
|  | | | | Stone, brick, cement | | | |  |  | | |  | | |  |
|  | | | | Don’t know | | | |  |  | | |  | | |  |
|  | | | |  | | | |  |  | | |  | | |  |
|  | | | | | | | |  |  | | |  | | |  |
|  | | | | | | | |  |  | | |  | | |  |
| 28. Did you get any food aid the last month? | | | | | | | | Yes |  | | |  | | |  |
|  |  |  | | |  | | | No |  | | |  | | |  |
|  |  |  | | |  | | | Don’t know |  | | |  | | |  |
|  |  |  | | |  | | |  |  | | |  | | |  |
| 29. How many meals did the family have yesterday | | | | | | | |  |  | | | meals | | |  |
|  |  |  | | |  | | |  |  | | |  | | |  |
|  |  |  | | |  | | |  |  | | |  | | |  |

| Annex 4 : RUTF for malaria recovery study |
| --- |
| **First and second follow up questionnaire (14 and 28 days)** |

| Study ID |  | | | |  | |  | | |  | | |
| --- | --- | --- | --- | --- | --- | --- | --- | --- | --- | --- | --- | --- |
| Sex | M | | F | |  | |  | | |  | | |
| Date (dd/mm/yy): |  | | | |  | |  |  | |  | | |
|  | | | | | | |  |  | |  | | |
| 1. Did the complaints of your child disappear in the last 2 weeks? | | | | | | |  |  | |  | | |
| If not, why do you think they didn’t? | | | | | | |  |  | |  | | |
|  | | | | | | |  |  | |  | | |
| 2. Has your child been ill with a **fever** at any time in the last 2 weeks? | | | | | | | Yes |  | |  | | |
|  | |  | |  | |  | No |  | |  | | |
|  | |  | |  | |  | Don’t know |  | |  | | |
|  | |  | |  | |  |  |  | |  | | |
| 3. Has your child had an illness with **cough** at any time in the last 2 weeks? | | | | | | | Yes |  | |  Q 4 | | |
|  | |  | |  | |  | No |  | |  Q 6 | | |
|  | |  | |  | |  | Don’t know |  | |  Q 6 | | |
|  | |  | |  | |  |  |  | |  | | |
| 4. When your child had an illness with a cough, did she/he breathe faster than | | | | | | | Yes |  | |  Q 5 | | |
| usual with short, rapid breaths or have difficulty breathing? | | | | | | | No |  | |  Q 6 | | |
|  | |  | |  | |  | Don’t know |  | |  Q 6 | | |
|  | |  | |  | |  |  |  | |  | | |
| 5. Was the fast or difficult breathing due to a problem in the chest or | | | | | | | Chest only | | |  | | |
| to a blocked or runny nose? | | | | | | | Nose only | | |  | | |
|  | |  | |  | |  | Both | | |  | | |
|  | |  | |  | |  | Don’t know | | |  | | |
|  | |  | |  | |  | Other; specify | | |  | | |
|  | |  | |  | |  |  |  | |  | | |
| 6. Has your child had **diarrhoea** in the last 2 weeks | | | | | | | Yes |  | |  | | |
| *(Explain the definition of diarrhoea: at least 3 or more liquid stools per day )* | | | | | | | No |  | |  | | |
|  | |  | |  | |  | Don’t know |  | |  | | |
|  | |  | |  | |  |  |  | |  | | |
| 7. In the last 2 weeks, has your child vomited everything? | | | | | | | Yes |  | |  | | |
| (persistent vomiting several times) | | | | | |  | No |  | |  | | |
|  | |  | |  | |  | Don’t know |  | |  | | |
|  | |  | |  | |  |  |  | |  | | |
| 8. Has your child visited a health facility since your previous visit? | | | | | | | Yes | |  | | |  |
|  | | | | | | | No | |  | | |  |
| 9. Which medication has your child taken since your previous visit? | | | | | | |  | |  | | |  |
| (other than the anti-malaria) | | | | | | | None | |  | | |  |
|  | | | | | | | Drug: | | | | |  |
|  | | | | | | |  | | | | |  |
| 10. Do you feel the child is completely recovered from the malaria episode? | | | | | | | Yes | | | | |  |
|  | | | | | | | No | | | | |  |
| If not, why do you think the child did not recover yet? | | | | | | | Don’t know | | | | |  |
|  | | | | | | |  | | | | |  |
|  | | | | | | |  | | | | |  |
|  | | | | | | |  | | | | |  |
| 11. **During the last 2 weeks** did she/he eat (food or breast milk)? | | | | | | | Much less | | | | |  |
| less then usual, about the same amount, or more than usual. | | | | | | | Somewhat less | | | | |  |
| *IF LESS, PROBE: Was he/she eating much less than usual or somewhat less* | | | | | | | About the same | | | | |  |
|  | | | | | | | More | | | | |  |
|  | | | | | | | Somewhat more | | | | |  |
|  | | | | | | | Much more | | | | |  |
|  | | | | | | | Don’t know | | | | |  |
|  | | | | | | |  | | | | |  |
|  | | | | | | |  | | | | |  |
|  | | | | | | |  | | | | |  |
|  | | | | | | |  | | | | |  |
| **ATTENTION: Question 12, 13 and 14 are only for the RUTF group on day 13** | | | | | | |  | | | | |  |
|  | | | | | | |  | | | | |  |
| 12. During the last 2 weeks how many days did your child eat 1 complete | | | | | | | ........ days | | | |  | |
| Plumpynut? | | | | | | |  | | | | |  |
|  | | | | | | |  | | | | |  |
| 13. How many plumpynut has your child eaten the last 14 days? | | | | | | |  | | | | |  |
|  | | | | | | |  | | | | |  |
| 14 How many empty sachets are returned? | | | | | | |  | | | | |  |
|  | | | | | | |  | | | | |  |

Thank you.

